## Introduction

Type 4 cardiorenal-anemia syndrome (CRAS) is defined as a pathophysiological disorder whereby chronic kidney disease (CKD) leads to chronic cardiac dysfunction and anemia (1). The vicious circle between heart failure, anemia, and kidney disease contributes to a significantly worse prognosis and high mortality (2). Cardiovascular disease (CVD) is the leading cause of death in patients with estimated glomerular filtration rate (eGFR) <60 ml/min per 1.73m^2^ (3), while anemia is an independent risk factor for CVD in CKD patients. Compared with hemoglobin between 120 and 129 g/L group, the risk of heart failure in CKD patients with hemoglobin <100g/L increases by 1.99 times (4). For every 10g/L reduction of hemoglobin in dialysis patients, the risk of left ventricular dilatation increased by 42%, and the risk of new/recurrent heart failure increased by 18% (5). Despite the high prevalence and significance of renal anemia (RA), its management strategies are far from satisfactory. In China, only 39.8% of RA patients received erythropoiesis-stimulating agents (ESAs) treatment, 22.7% of patients initiated anemia-correction when hemoglobin decreased to less than 70 g/L, and only 8.2% of patients achieved a target hemoglobin of 110–120 g/L (6). Because of this, anemia-correction seems to be a reasonable approach to treat type 4 CRAS. ESAs together with iron supplements are conventional treatments for RA. Unfortunately, it was confirmed by the reduction of events by darbepoetin alfa in heart failure (RED-HF) study (7) that treatment with ESAs did not improve clinical outcomes in patients with systolic heart failure and mild-to-moderate anemia. On the contrary, the use of ESAs equivalent to more than 10,000 U/week of recombinant human erythropoietin (rHuEPO)/epoetin alfa will increase the risk of hypertension, stroke, thrombosis, thrombolysis in hemodialysis vascular access, and all-cause mortality (8). Iron overload due to excessive iron supplements also resulted in an increased risk of cardiovascular morbidity and mortality among hemodialysis patients (9). There is an urgent need to develop a safe and effective treatment for CRAS.

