### Intervention

Eligible participants will be randomly assigned in a 1:1 ratio to receive either roxadustat or erythropoietin for 24 weeks.

All participants will receive optimized treatments for heart failure and renal anemia based on the 2019 ESC (16) and 2012 KDIGO practice guidelines. The detailed treatments are listed as follows:

(1) Treatment of heart failure: All participants will be recommended to take angiotensin-converting enzyme inhibitors (ACEIs)/angiotensin receptor blockers (ARBs), beta blockers, aldosterone blockers, or angiotensin receptor-neprilysin inhibitor (ARNi) as basic treatment for HF. The individualized strategy regarding the types and dosages of drugs will be obtained by their physicians. In order to reduce the adverse events of hyperkalemia and deterioration of renal function, ACEIs/ARBs administration should be avoided in patients with CKD stage 5 (eGFR <15 mL/min/1.73 m^2^), and ARNi administration should be avoided in patients with CKD stage 4 or 5 (eGFR <30 mL/min/1.73 m^2^), especially for patients with a serum potassium > 5 mmol/L. When the patients' serum potassium levels reach as high as 5.5 mmol/L, ACEIs/ARBs or ARNi should be halted.(2) Iron deficiency treatment: All participants will receive 60 mg of oral elemental iron daily, with dose titration every 4 weeks to achieve a target transferrin saturation (TSAT) between 20 and 40%, as well as serum ferritin (SF) between 100 and 300 μg/L. The dose should be decreased if TSA > 50% or/and SF > 300 μg/L. If oral iron therapy is ineffective or intolerable after a 4-week treatment period, participants will be prescribed intravenous sucrose iron 100 mg/time, three times a week, and TSAT and SF will be evaluated again after a cumulative dosage of 1,000 mg.

Erythropoietin group

The erythropoietin (EPO) group will be treated with rHuEPO at an initial dose of 100–150 U/kg/week, divided into 2–3 subcutaneous injections, or 10,000 IU subcutaneously once weekly, with no restriction on the manufacturer of rHuEPO. The goal of initial EPO treatment is to increase hemoglobin by 10–20 g/L per month. The dose of rHuEPO can be increased by 60 U/kg/week, to maintain a target hemoglobin ranging from 100 to 120 g/L.

Roxadustat group

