Participants randomized to roxadustat group will receive oral roxadustat (FibroGen, Co. Ltd, H20180024), with an initial dose of either 70 mg (body weight between 40 and 60 kg) or 100 mg (body weight ≥ 60 kg), 3 times a week. Based on the results of phase III clinical study of roxadustat in non-dialysis Chinese patients (17), the dose will be adjusted every 4 weeks following the rule displayed in Table 2, to maintain a hemoglobin level between 100 and 120 g/L.

**Table 2 T2:** Dose adjustments of roxadustat.

**Δhemoglobin over the past 4 weeks (g/L)**	**Hemoglobin level (g/L)**			
	** <100**	**100– <110**	**110– <120**	**≥120**
< –10	Increase	Increase	No change	Hold, then resume dosing when hemoglobin <110 g/L at a dose that is reduced by 1 dose steps
–10 to 10	Increase	No change	Decrease	
>10	Increase	Decrease	Decrease	

*Investigator will adjust the dose in dose steps of 50, 70, 100, 120, 150, and 400 mg. The dose can be changed 1 step at a time, and the maximum dose is 2.5 mg/kg. Δhemoglobin, change in hemoglobin*.

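### The roxadustat dose steps in the Table 2 footnote contradict the 2.5 mg/kg maximum beside them: the 400 mg step fits only at 160 kg or more

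*Protocol article*

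**What the plan says.** **Roxadustat (Intervention, Table 2 and its footnote).** The footnote gives the ladder: "Investigator will adjust the dose in dose steps of 50, 70, 100, 120, 150, and 400 mg". Its next sentence sets the pace and the limit: "The dose can be changed 1 step at a time, and the maximum dose is 2.5 mg/kg". Participants begin "with an initial dose of either 70 mg (body weight between 40 and 60 kg) or 100 mg (body weight ≥ 60 kg"), three times a week, and "the dose will be adjusted every 4 weeks following the rule displayed in Table 2". Table 2 calls for an increase in all three of its rows whenever hemoglobin is below 100 g/L. The Inclusion Criteria admit only patients with hemoglobin from 70 to below 100 g/L.

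**Erythropoietin (Intervention, Erythropoietin group).** Treatment starts with "rHuEPO at an initial dose of 100–150 U/kg/week, divided into 2–3 subcutaneous injections, or 10,000 IU subcutaneously once weekly". On adjustment the text says: "The dose of rHuEPO can be increased by 60 U/kg/week, to maintain a target hemoglobin ranging from 100 to 120 g/L".

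**Introduction.** As part of the case for the trial, the article states that "the use of ESAs equivalent to more than 10,000 U/week of recombinant human erythropoietin (rHuEPO)/epoetin alfa will increase the risk of hypertension, stroke, thrombosis" and other harms, including all-cause mortality.

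**The concern.** The step list and the maximum stand in adjacent sentences of one operative dosing instruction, and they give different answers to the question of which doses are available. The list offers 400 mg as the step after 150 mg. The maximum rules that step out for anyone below 160 kg.

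The step is not a remote one. From the 100 mg start it is the third increase, and every participant enters in the hemoglobin column where Table 2 says to increase. A patient who responds slowly could be due for it by week 12 of the 24-week treatment period.

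Two things are at stake. The first is a dosing error made from the printed table. The second is that the experimental treatment is not defined uniquely: two investigators could read the footnote differently and treat similar patients differently.

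A smaller matter concerns the comparator. The Introduction names a weekly erythropoietin dose above which it says risk rises, and the dosing under Intervention can pass that level at ordinary adult weights without the article commenting on it.

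**Working it through.** The article prints no derived figure on this point, so there is nothing to reproduce. The check is arithmetic on the stated doses.

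**Inputs.** Steps of 50, 70, 100, 120, 150 and 400 mg, maximum 2.5 mg/kg, one step at a time (Table 2 footnote). Starts of 70 or 100 mg by weight, adjustment every 4 weeks (Intervention). Erythropoietin start of 100–150 U/kg/week or 10,000 IU once weekly, increases of 60 U/kg/week (Intervention). Level of 10,000 U/week (Introduction). The article gives no distribution of body weight, so all weights below are assumptions shown as a range.

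**Unit of the maximum.** It is read as applying to each administered dose, as the steps do. A weekly reading would make the starting dose itself a breach: 3 × 100 mg / 60 kg = 5.0 mg/kg.

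**1. Lowest weight at which each step is within the maximum** (step / 2.5)

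| Step (mg) | Lowest weight (kg) | Ratio to previous step |
|---|---|---|
| 50 | 20 | – |
| 70 | 28 | 1.40 |
| 100 | 40 | 1.43 |
| 120 | 48 | 1.20 |
| 150 | 60 | 1.25 |
| 400 | 160 | 2.67 |

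**2. What 400 mg means at assumed weights**

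| Weight (kg) | Maximum, 2.5 × weight (mg) | Largest listed step within it (mg) | 400 mg in mg/kg |
|---|---|---|---|
| 60 | 150 | 150 | 6.67 |
| 80 | 200 | 150 | 5.0 |
| 100 | 250 | 150 | 4.0 |
| 120 | 300 | 150 | 3.33 |
| 160 | 400 | 400 | 2.5 |

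From 60 kg to just under 160 kg the largest step within the maximum stays at 150 mg, although the maximum itself rises from 150 mg to nearly 400 mg.

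**3. How soon the step list reaches 400 mg.** From 100 mg the increases are 120, 150, 400: three increases at 4-week intervals, so 3 × 4 = week 12 at the earliest. From 70 mg there is one more, so 4 × 4 = week 16.

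**4. Erythropoietin against 10,000 U/week** (threshold weight = 10,000 / dose in U/kg/week)

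| | 100 U/kg start | 150 U/kg start |
|---|---|---|
| At start | 10,000/100 = 100 kg | 10,000/150 = 66.7 kg |
| After one increase | 10,000/160 = 62.5 kg | 10,000/210 = 47.6 kg |

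Above these weights the weekly dose exceeds 10,000 U. Weekly totals at assumed weights, from the low to the high starting dose:

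- 40 kg: 4,000–6,000 U at start; 6,400–8,400 U after one increase.
- 60 kg: 6,000–9,000 U at start; 9,600–12,600 U after one increase.
- 80 kg: 8,000–12,000 U at start; 12,800–16,800 U after one increase.

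The flat start of 10,000 IU sits exactly at the level, so any increase passes it (at 60 kg, 10,000 + 60 × 60 = 13,600 U).

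**The case against.** The best defense of the roxadustat rule is that the maximum stands right beside the ladder. Read together, the two sentences bar 400 mg below 160 kg, so the instruction does not direct anyone past the maximum. The entry may simply be a misprint. This stands as far as it goes: a reader might infer that Table 2 mandates a breach, and it does not. But a safeguard that works only if the reader overrides the sentence before it leaves the contradiction in place. Nor can condensation into an article explain it, because both statements are printed.

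Three stronger readings are tempting, and the document supports none of them.

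- **That both arms break a ceiling.** Only roxadustat has one. The 10,000 U/week figure is a cited statement about risk in the Introduction, and the article sets no erythropoietin limit for the trial.
- **That erythropoietin can only be increased.** The text mentions only an increase, but in permissive terms, toward a hemoglobin range with an upper bound, and it places anemia care in both arms under a named KDIGO guideline. Rules for reducing or holding the dose may be in the full protocol. Silence in an article does not show that they are missing.
- **That unequal titration rules will bias the comparison in favor of roxadustat.** Two different drugs need not share an algorithm, both arms state the same 100–120 g/L target, and nothing in the article allows the size of such a bias to be estimated. Change in hemoglobin is already a secondary outcome and blood pressure a safety measure, so a difference in control would be visible.

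The erythropoietin arithmetic also depends on weight and starting dose: at 60 kg, the low start plus one increase stays at 9,600 U/week.

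**Conclusion.** The contradiction in the Table 2 footnote is real and exact. The 400 mg step and the 2.5 mg/kg maximum agree only at 160 kg or more. Between 60 kg and that weight nothing listed above 150 mg is usable, and taking the step list alone would give 2.67 times the previous dose and, at an assumed 80 kg, twice the maximum. The result rests on no statistical assumption, only on reading the maximum per administered dose. How many participants could meet the conflict is unknown, because no weights or response rates are given. It needs correction because it is an operative dosing instruction, not because a breach has been shown.

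The erythropoietin point is minor. The dosing can pass the level that the Introduction associates with harm, at weights that depend on the starting dose and the number of increases. This is a tension between the trial's rationale and its comparator regimen, and no trial limit is exceeded.

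**What to change.** The sponsor's clinicians should reconcile the list of dose steps with the 2.5 mg/kg maximum and reissue Table 2 with its footnote, so that the two sentences give one answer at every body weight. Which entry is wrong, and what should replace it, is for them to decide. Recruitment had already begun when the article was written, so they should also confirm that the dosing instructions in use carry the reconciled text.

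In the same revision, check the Introduction's statement on weekly erythropoietin dose against the Erythropoietin group paragraph, so that a reader can see how the two fit together.

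The cost is one corrected table footnote, by amendment if the full protocol carries the same wording, and possibly a sentence on the comparator. Sample size, outcomes and analysis are not affected.

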### Outcome Measurement

Primary outcomes

The trial is designed to evaluate the improvement of heart function by roxadustat. Therefore, mean change in the brain natriuretic peptide (BNP), 6-min walk test (6-WT), and left ventricular ejection fraction (LVEF) estimated by echocardiography from baseline to 24 weeks will be applied as primary outcomes.

Secondary outcomes

(1) All-cause death and cardiovascular death.(2) Cardiovascular events including non-fatal acute myocardial infarction and non-fatal stroke.(3) Hospitalization regarding heart failure.(4) Change in Minnesota Living with Heart Failure Questionnaire (MLHFQ) score from baseline to 24 weeks.(5) Progress of cardiac function assessed by NYHA classification from baseline to 24 weeks.(6) Echocardiographic parameters including left ventricular diastolic diameter and volume (LVDD and LVDV) and ventricular mass (LVM).(7) Change in anemia-related parameters including the hemoglobin level, hemoglobin response rate (proportion of patients with hemoglobin elevation ≥ 10 g/L), serum iron, SF, TSAT, and hepcidin from baseline to 24 weeks.(8) Change in inflammatory parameters including high-sensitivity C-reactive protein (hs-CRP), procalcitonin (PCT), interleukin-6 (IL-6), tumor necrosis factor a (TNF-a), and lipoprotein a [Lp (a)] from baseline to 24 weeks.(9) Safety assessment consists of blood pressure, blood routine, urine routine, alanine aminotransferase (ALT), aspartate aminotransferase (AST), alkaline phosphatase (ALP), gamma-glutamyl transpeptidase (GGT), serum total bilirubin (TBIL), serum potassium, serum sodium, serum chlorine, and electrocardiogram.

### Adverse Events

Adverse events (AEs), comprising the precise time of occurrence, severity, duration, processing, and prognosis, will be recorded in the case report form at every study visit, and their correlation with the study medications will be assessed. The severity of AEs will be classified into mild, moderate, and severe. Severe AEs will be reported to the principal investigator and the ethics committee.

## Discussion

The concept of CRAS, formerly known as cardio renal syndrome, has gained considerable interest over the last decade (19). Despite worldwide concern, the mechanistic framework of CRAS remains to be illustrated, and there is a lack of effective treatment (20). Several pilot or small sample studies (21, 22) indicated that ESAs alone or combined with iron supplement could reduce BNP and cardiovascular hospitalization in CKD patients with anemia and heart failure. Unfortunately, these findings were overturned by converse results of well-designed and large sample clinical trials (23). In the 2021 ESC guideline for heart failure, ESAs were excluded from the treatment of heart failure related anemia (24). Although the underline mechanism has not been elucidated, it is suggested that exogenous erythropoietin generated by ESAs can largely increase C-terminal fibroblast growth factor 23 (FGF23) level (25), which is significantly associated with left ventricular hypertrophy and an increased risk of mortality. Roxadustat is an oral anemia-correction agent function that increases endogenous erythropoietin by inhibiting propyl hydroxylase induced hypoxia-inducible factor degradation (26). With the advantages of endogenous erythropoietin generation and FGF23 lowering (27), roxadustat is a reasonable candidate in CRAS treatment, but there is a lack of relevant clinical evidence in this regard. Moreover, roxadustat may have additional effects of cholesterol-lowering (10) and could protect experimental animal from myocardial ischemia-reperfusion injury (28). It is reasonable to assume that roxadustat is a promising agent for CRAS with multiple mechanisms involved. This study will be the first attempt to evaluate the potential benefit of roxadustat in patients with CRAS.

Former studies that focused on anemia-correction in CRAS mainly included patients with mild anemia, and the target hemoglobin level reached as high as 130 g/L. High hemoglobin levels might be partially responsible for adverse events such as stroke, hypertension, and thrombosis (29). In this study, we will recruit patients with a much lower hemoglobin level of 70–100 g/L, who will benefit more from anemia-correction. To decrease the incidence of adverse events resulting from excessive increase of hemoglobin, the target hemoglobin level in this study will be 100–120 g/L.

BNP and N-terminal pro-B-type natriuretic peptide (NT-proBNP) have been shown to be independent predictors of mortality (all-cause and cardiovascular) in advanced heart failure despite different cutpoints, time intervals, and prognostic models. In this study BNP is designed as one of the primary outcomes and is used as surrogate to calculate the study sample size, while NT-proBNP, with a relatively longer plasma half-life, is adopted as a surrogate in plenty of clinical trials. So, we think either BNP or NT-proBNP is acceptable as a prognostic marker of CHF.

As an open-label study, both the participants and investigators will be aware of the assignment and treatment. To ensure the quality of this study and minimize bias, the analysis of data will be performed by an independent statistician who is not involved in the study and blind to the allocation of treatment.

There are some limitations to this study. First, the study is single-centered and open-labeled, indicating there might be increased bias. Second, since most of the participants are unlikely to reach hard clinical endpoints, such as all-cause mortality or cardiovascular mortality, in the short study duration of 36 weeks, primary outcomes only include surrogate endpoints.

We expect that the results of this study will provide a scientific rationale for the use of roxadustat in improving the heart function of type 4 CRAS.

## Ethics Statement

The studies involving human participants were reviewed and approved by the Ethics Committee of Beijing Hepingli hospital. The patients/participants provided their written informed consent to participate in this study.

